### Trial

This is a monocentric, prospective, explorator, non-randomized, and non-blinded diagnostic study. Patients enrolled are prospectively followed from inclusion to surgery, with all imaging procedures performed within a predefined preoperative window. All participants undergo a predefined multimodal imaging workflow including multiple diagnostic modalities, incorporing contrast-enhanced CT, mpMRI (including MRE) and US-E, aiming to explore the diagnostic potential of these techniques in the characterization of renal tumors and renal-parenchyma.

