### Study population

The study will enroll 50 patients with renal tumors referred for surgical management at the University Hospital of Bordeaux. Patients eligible for inclusion must be at least 18 years old or older, scheduled for nephrectomy for renal neoplasm within the Urology Department, and have a planned or available multiphasic CT as part of their preoperative workup. Participants must also provide informed consent for inclusion in the UroCCR cohort and participation in the Rein-3D Print Mechanics study, with the condition that they are affiliated with social security system. Exclusion criteria include pregnancy or breastfeeding, contraindications to MRI or gadolinium-based contrast agents, previous renal biopsy <15 days before MRI, and certain comorbidities such as obesity (body mass index (BMI) ≥ 30 kg/m²), thoracolumbar spinal fixation, or the presence of small (<2 cm) cystic or necrotic renal tumors with a solid component. Additionally, patients with ascites, legal protection measures, or difficulty in understanding and expressing themselves in French will be excluded.

All study data will be recorded in the imaging systems (Carestream PACS; Philips) and UroCCR database, managed by the CREDIM (Centre de Recherche et Développement en Informatique Médicale) at the University Hospital of Bordeaux. The database is authorized by the French Data Protection Authority (CNIL; authorization DR-2013–206, request n°912578) and operates under the national MR-001. The study involves senior urologists, expertised radiologists from the uro-vascular imaging department, the reference pathologist, biomedical engineers, data managers and biostatisticians.

Data entry was performed by trained personnel, and clinical variables were coded using standard dictionaries (MedDRA, ATC). Data quality was ensured through automated checks and query resolution. All data were pseudonymized, securely stored, and transferred via a protected platform when required. Confidentiality was maintained in accordance with regulatory standards, and study data were archived for 20 years.

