### Outcome measures

The primary outcome of this study is to develop a predictive model of biomechanical properties of both normal and pathological renal tissue, using MRE as the reference, based on density values from multiphasic CT. All analyses will be conducted before the definitive histological diagnosis.

The secondary outcomes are:

Multimodal correlation: to correlate elasticity values obtained by MRE, and ultrasound elastography with CT density values, on a voxel to voxel, ROI to ROI, and anatomical region basis across all CT acquisition phases.Feasibility of DWI-vMRE: This study aims to assess the feasibility and optimization of parameters for DWI-vMRE using a clinical 1.5-Tesla MRI scanner. It will focus on evaluating key performance metrics, including image quality (qualitative assessment), contrast-to-noise ratio (CNR), signal-to-noise ratio (SNR), and the identification and documentation of artifacts.Feasibility of elastography modalities: to assess the feasibility of MRE, and US–E for quantifying renal parenchymal and tumoral stiffness, and to identify limiting factors (e.g., BMI, sarcopenia, lesion location, size, and architecture), including enumeration of non-diagnostic examinations.Repeatability analysis: to evaluate the repeatability of MRE, and US-E across the cohort and within subgroups defined by patient morphotype and tumor characteristics, using intraclass correlation coefficients and Bland–Altman plots.De-correlation and bias analysis: to identify situations of de-correlation or potential biases between biomechanical measurements obtained from MRE and US-E (e.g., extreme elasticity values, morphotype-related limitations).Histopathological associations: to assess associations between biomechanical properties (measured or CT-predicted) and final histological subtype; and, for clear cell renal cell carcinoma, with histological grade. This includes ROC curve analyses and identification of potential diagnostic cutoff values.

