### Statistical analysis

Imaging data will be acquired across multiple modalities, including MRE (μMRE), US-E, and CT (dCT, dCT40s, dCT90s, dCT10min), alongside clinical and morphological variables such as BMI, sarcopenia, lesion size, volume, location, histological type, malignancy status, and histological grade for clear cell renal carcinoma, where applicable. Quantitative variables will be extracted and analyzed for each region of interest (ROI). Descriptive statistics will summarize categorical variables as frequencies and percentages, while continuous variables will be presented as mean, standard deviation, median, range, and interquartile range.

The primary objective is to develop a regression model to predict μMRE based on CT-derived density values. The dataset will be divided into a 70% training set and a 30% test set, and various regression algorithms (linear regression, elastic net, k-nearest neighbors, support vector machines, random forests, and artificial neural networks) will be compared using repeated nested cross-validation. Model performance will be evaluated based on coefficient of determination (R²), mean squared error (MSE), and root mean squared error (RMSE), with RMSE serving as the primary criterion for model selection. Reproducibility of MRE measurements will be assessed through repeated acquisitions, with the highest-quality sequence selected for model development.

Secondary analyses will investigate the interrelationships between biomechanical parameters across imaging modalities. Spearman’s rank correlation coefficient will be used to assess correlations between elasticity values from MRE, US-E, and CT densities. The feasibility and image quality of DWI will be evaluated using a five-point qualitative scale, contrast-to-noise ratio, signal-to-noise ratio, and systematic reporting of artifacts. Non-diagnostic examinations and potential limiting factors—such as patient morphotype, sarcopenia, and lesion characteristics—will be documented. The repeatability of elastography measurements will be quantified using intraclass correlation coefficients and Bland-Altman plots. Cases of modality de-correlation will be explored through paired scatterplots and descriptive analysis of discordant data points.

The final statistical analysis plan will be reviewed and approved by the Scientific Committee prior to database lock.

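### The stated method for finding where MRE and US-E disagree cannot separate bias at extreme stiffness from regression to the mean (minor)

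*Protocol article*

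**What the plan says.** In the protocol article, Outcome measures lists a de-correlation and bias analysis among the secondary outcomes. Its aim is to identify "situations of de-correlation or potential biases between biomechanical measurements obtained from MRE and US-E (e.g., extreme elasticity values, morphotype-related limitations").

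Statistical analysis gives the method for that aim in one sentence: "Cases of modality de-correlation will be explored through paired scatterplots and descriptive analysis of discordant data points".

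Two neighbouring analyses touch the same data:
- Across modalities, Spearman's "rank correlation coefficient will be used to assess correlations between elasticity values from MRE, US-E, and CT densities".
- Within a modality, "The repeatability of elastography measurements will be quantified using intraclass correlation coefficients and Bland-Altman plots". Outcome measures likewise assigns these two tools to repeatability, in the cohort and in subgroups by morphotype and tumour characteristics. Neither section assigns them to MRE against US-E.

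BMI, sarcopenia, lesion size and lesion location are listed among the recorded variables. The final analysis plan is still to be approved before database lock.

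**The concern.** The aim has two parts: whether the two methods diverge at certain stiffness levels, and whether divergence goes with certain patient or lesion traits. The stated method is weak for both.

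**Stiffness level.** Both methods carry random error. A reading that is extreme on one is, on average, less extreme on the other, even when neither is biased. A scatterplot of one against the other invites the reader to judge extremeness along a single axis, and extreme elasticity is one of the situations the protocol article expects to find.

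**Traits.** To say that high BMI or a given location goes with disagreement, one must know how often that trait occurs among pairs that agree. A description of the discordant points does not supply that comparison by itself.

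At stake is a published statement that MRE and US-E part company at extreme stiffness, or in certain patients, when measurement error could give the same picture. MRE is the reference for the primary model, so readers may give such a statement weight, although nothing in the protocol article feeds this outcome into that model.

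**Working it through.** The protocol article gives no agreement limit, no MRE/US-E correlation and no figure on this point, so there is nothing to reproduce. The check asks how large the artefact is under a model with no bias at all.

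**Inputs.** From the protocol article: 50 patients (Study population). Assumed: standardised readings X (MRE) and Y (US-E), bivariate normal, equal scale, equal independent errors, no bias, correlation r from 0.4 to 0.9; for samples of 50, one pair per patient.

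**Step 1: mechanism.** Let D = X − Y, so SD(D) = √(2(1 − r)). Flag a pair as discordant if |D| > 1.96 × SD(D), which flags 5% overall. Given X = x, D has mean (1 − r)x and variance 1 − r².

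At r = 0.6 the limit is 1.96 × √0.8 = 1.753 and the conditional SD is √0.64 = 0.8.
- At x = 0: P(|Z| > 1.753/0.8 = 2.19) = 2.8%.
- At x = 1.645: the mean of D is 0.658, so P(Z > 1.095/0.8 = 1.37) + P(Z < −2.411/0.8 = −3.01) = 8.5% + 0.1%, about 8.7% before rounding.

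The flag rate rises with |x| although there is no bias.

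**Step 2: flag rates by level of one modality** (simulation, 2,000,000 pairs per r). Extreme means |X| > 1.645 (10% of pairs); the middle half is |X| < 0.674. The rate in all non-extreme pairs follows as (5% − 0.10 × extreme rate)/0.90.

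| r | Extreme 10% | Middle half | All non-extreme |
|---|---|---|---|
| 0.4 | 16.7% | 2.3% | 3.7% |
| 0.6 | 12.8% | 3.1% | 4.1% |
| 0.8 | 8.9% | 4.1% | 4.6% |
| 0.9 | 6.9% | 4.5% | 4.8% |

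**Step 3: starting from the discordant points**, which is the order of work the protocol article describes. At r = 0.6, 51% of flagged pairs contain an extreme reading on at least one method, against 17% of all pairs.

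**Step 4: samples of 50.** Among the five most discordant pairs, the share containing a top-five or bottom-five reading on either method is about 65% at r = 0.6 and 49% at r = 0.8; the base rates are 32% and 29%. The false pattern of MRE above US-E in the five highest MRE readings and below it in the five lowest appears in 93% of samples at r = 0.6 and 80% at r = 0.8. Ranked on the two-method mean, it appears in about 25%, which is what two unrelated signs give (0.5 × 0.5).

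**Step 5: does the two-method mean remove it?** With M = (X + Y)/2 and error variances a and b, Cov(D, M) = (a − b)/2.
- Equal errors: the covariance is zero, and the flag rate is 5% at every level.
- Errors 0.2 and 0.4 of the true variance: Cov = −0.1, Var(D) = 0.6, Var(M) = 1 + 0.6/4 = 1.15, so the correlation is −0.1/√(0.6 × 1.15) = −0.12.
- Errors 0.2 and 0.8: extremes of the mean are flagged at 7.9%, the middle half at 4.3%.

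So the mean removes the artefact fully only when the errors are equal. Otherwise a smaller one remains, whose size depends on the two error variances. The planned repeatability analysis estimates these.

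**The case against.** The strongest reply is that the simulation supplies rules the protocol article does not state: discordance as a raw difference, and extremeness judged on one modality. The result depends on both. If discordance is departure from a fitted trend of US-E on MRE, MRE extremes are flagged at 5.0% at r = 0.6, the same as the middle half. That is correct, but the over-representation then moves to the US-E axis, so the problem is relocated rather than removed. Definitions of discordant and extreme belong in the analysis plan, which is not shown, and their absence is not criticised here. The point is that the stated method, as far as it goes, does not fit the stated aim.

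Three stronger readings may tempt a reader, and the protocol article does not support them:
- **That only discordant points are looked at.** The paired scatterplots and the Spearman analysis are not limited to them. The limitation applies to the descriptive step.
- **That extreme values are bound to be discordant, so that the plan manufactures its own example.** At r = 0.6, 87.2% of MRE extremes (100% − 12.8%) are not flagged. With one pair per patient, about 50 × 0.10 × 0.128 = 0.6 flagged MRE extremes would be expected. Extremes are over-represented, and only when read from a single modality.
- **That nothing would allow traits to be compared.** Cohort summaries of BMI, sarcopenia and lesion variables give base rates, limiting factors are documented, and repeatability is examined in subgroups. What is not stated is a comparison of discordant with concordant pairs.

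It is also fair that the fourfold contrast at r = 0.6 uses the middle half as comparator; against all non-extreme pairs it is about threefold (12.8/4.1). Finally, the outcome is secondary and descriptive, with no test or threshold announced. That lowers the stakes but does not make the method suit its aim.

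**Conclusion.** The point holds in a limited form and is minor. Paired scatterplots and a description of discordant points are poorly suited to deciding whether MRE and US-E diverge at extreme stiffness, because regression to the mean gives the same appearance without bias when extremes are read from one modality. The description also does not by itself set discordant pairs against concordant ones.

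Under equal-scale, equal-error, unbiased methods the artefact is material for correlations up to about 0.8 and small near 0.9. Those correlations are assumptions, as are equal scale, equal errors and one pair per patient. No claim is made that the trial will report a false finding, or that the primary model is affected.

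**What to change.** In Statistical analysis, or in the analysis plan still to be approved, put the following before the description of discordant cases:

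1. For all MRE/US-E pairs, expressed on a common scale, plot the difference against the mean of the two methods.
2. Judge discordance, and any trend of the difference with stiffness, against the repeatability error of each modality. State that unequal error variances leave some trend even without bias.
3. Compare the traits already recorded (BMI, sarcopenia, lesion size and location) across all pairs, allowing for several regions from the same patient.

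Discordant cases can then be described as now planned. A formal regression on several factors is optional and would be ambitious with 50 patients.

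The cost is a few sentences and slightly more analysis. No new data are needed, because the repeatability measurements and the traits are already part of the study.

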## Expected results

This protocol introduces a multimodal evaluation model that integrates several imaging techniques, including CT, MRI and US-E. Despite their routine clinical use, their comparative value and the degree of complementarity among them have not been systematically examined in the same patients within a standardized preoperative interval. By generating voxel-level and ROI-level based datasets across modalities, the study will enable a level of correlation analysis that has not previously been possible.

A key strength of the study is its ability to associate all imaging measurements. This unique design reduces the ambiguity inherent in isolated imaging biomarkers and supports the development of a CT-based predictive model that could be broadly applicable, given the near-universal availability of multiphasic CT (Fig 3).

### Monitoring

A Scientific Advisory Board met annually to oversee study conduct, ensuring protocol compliance, ethical standards, and study progress, and advising on modifications or continuation. No independent monitoring committee was established due to the low-risk nature of the study but could be implemented if needed. Substantial protocol amendments requiring changes affecting participant safety, study validity, or conduct were approved by the sponsor and relevant ethics and regulatory authorities (CPP, ANSM) prior to implementation, while non-substantial modifications were notified to the ethics committee. Investigators were informed of all changes, and updated consent was obtained when required.
